#### Clinical laboratory parameters and abnormal laboratory test results

The results of all laboratory tests required by the protocol will be recorded. All clinically important abnormal laboratory tests occurring during the study will be repeated at appropriate intervals until they return either to baseline or to a level deemed acceptable by the investigator or until a diagnosis that explains them is made. The criteria for determining whether an abnormal laboratory test result should be reported as an AE are as follows:

1. Test result is associated with accompanying symptoms, and/or.

2. Test result requires additional diagnostic testing or medical/surgical intervention, and/or.

3. Test result leads to a change in study dosing or discontinuation from the study, significant.

additional concomitant drug treatment or other therapy, and/or.

4. Test result leads to any of the outcomes included in the definition of a SAE, and/or 5. Test result is considered to be an AE by the investigator.

The following tests will be completed at the screening and baseline visits: blood chemistry (including sodium, potassium, chloride, BUN, creatinine, glucose, SGOT, SGPT, LDH, alkaline phosphatase, total bilirubin, cholesterol, and triglycerides) and complete blood count. In the event of clinically significant abnormalities, urine samples will be sent for urinalysis. Moreover, the following additional lab tests will be carried out at screening, baseline, week 13, week 24 and week 52 (HbA1c, fasting glucose, total cholesterol, HDL, LDL, triglycerides, insulinemia, albumin to creatinine ratio, and plasma creatinine).

## Results

In total, 300 subjects have been randomized to the varenicline (*n* = 150) or placebo (*n* = 150) groups with 194 subjects completing the study at week 52; 100 in the varenicline group and 94 in the placebo group. The conduct phase of the study is completed, while data cleaning and analyses are ongoing.

## Discussion

Smoking and diabetes is a dangerous liaison and promoting smoking cessation for those with diabetes must be a top priority [8]. There is a pressing need for efficient interventions to reduce or prevent morbidity and mortality in smokers with DM. The high-affinity α4β2 nicotinic acetylcholine receptor partial agonist varenicline has been shown to to be effective for smoking cessation in smokers [19, 20], including those with cardiovascular disease [21].

COPD [22], or depression [23]However, there is very limited data about its efficacy and safety in smokers with diabetes [35], and a clinical trial of varenicline targeted specifically at smokers with T2DM is warranted to better inform medical/health authorities (FDA, EMEA) and physicians worldwide. To gather such evidence we will conduct the first randomized, double blind, placebo-controlled study of efficacy and safety of varenicline (1 mg BID) in smokers with T2DM.

The study protocol adopts a number of measures that contribute to quality of the study.

The gold standard to rigorously assess smoking cessation success in drug trials is continuous abstinence. Consistent with previous varenicline RCTs [25–27] and the Society for Research on Nicotine and Tobacco recommendations [28], we have adopted.

CAR as a robust primary efficacy end point. Although smoking abstinence will be self-reported, objective biochemical validation by measurements of exhaled carbon monoxide levels with a calibrated CO meter will be mandatory at each study visit.

The RCT study design with extended follow-up at 52 weeks will provide a robust answer to determine the safety and long-term efficacy of varenicline in T2DM. The length of the study was based on the consideration that substantial changes in the primary endpoint (CAR 12-week) could be reasonably observed early in the course of the trial. It is however likely that a much longer follow-up period is necessary to firmly establish findings consistency over time, hence study duration is extended to 52 weeks. Clearly, randomization will equalize variation in smoking history and other variables between study arms, thus ensuring high quality data.

Importantly, the entire study is designed keeping the welfare of all participants at its center; at every contact participants will be counseled to stop smoking by experienced clinical psychologists. Therefore, the potential long-term benefit of participating in this study is—under a best case scenario—to completely stop smoking even after completion of study follow-ups.

Compliance with the study protocol is critical as failure to regularly take varenicline would reduce or nullify the expected quit rates as well as produce inaccurate safety reporting. Besides, being instructed on the importance of adhering to their randomized product allocation, participants will be asked to report any non-compliance via a study diary and will be informed that biochemical verification of compliance and assessments checks of adherence will be conducted at each clinic visits. Strict adherence to the study protocol should be also aided by frequent weekly visits for drug checks, during which participants will be asked to return all empty, part-used, and unused blinded bottles (containing study drugs/placebo). Any non-compliance will be recorded in the study diary after counting all empty, part-used and unused bottles. Although not expected that compliance for this study will be materially different compared to other comparable studies, our power calculations are over-estimated to take this into account. Of note, non-compliance to study products is in itself an interesting outcome and we will be able to assess the impact of different level of non-compliance on smoking cessation rates.

Our study has limitations and may face challenges.

First, due to the relatively long duration of the study (52-weeks), maintaining a sufficient level of subject retention may be a challenge. Nonetheless, trial attendance and retention is likely improved by inviting participants to return to the clinic for their free supply of study drugs, by offering a dedicated fast track approach for their outpatient clinic appointments and by providing tailored counseling.

Second, the results cannot be generalized to all diabetic patients who smoke. We will recruit a (ambulatory) population of diabetic smokers who have been stably treated for T2DM. Therefore, the study protocol excludes smokers with untreated disease and T1DM smokers. Moreover, the study protocol excludes smokers with diagnosed depression or taking antidepressant medications. Therefore, the study cannot address the safety or efficacy of varenicline in smokers with comorbid depression, which occurs at a higher rate in smokers with diabetes than in the general population of smokers [36].

The results of this RCT with varenicline will help determine whether an optimally varenicline-treated cohort of T2DM patients who smoke will experience significant success rates, without causing side effects.

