## Abstract

Reducing exposure to cigarette smoke is an imperative for public health and for diabetic patients. Patients with diabetes who continue to smoke face challenges at quitting and the delivery of effective smoking cessation interventions is a major unmet need. The high-affinity α4β2 nicotinic acetylcholine receptor partial agonist varenicline in combination with counseling is effective for smoking cessation, but evidence in patients with diabetes is limited. A clinical trial of varenicline targeted specifically at smokers with T2DM is warranted. This randomized, double blind, placebo-controlled trial will be the first study to test efficacy and safety of varenicline in smokers with type 2 diabetes mellitus (T2DM) over the course of 52 weeks. We hypothesize that varenicline treatment (1 mg BID, administered for 12 weeks) would increase quit rates, maintain smoking abstinence up to 1 year after treatment, and be well-tolerated in T2DM smokers intending to quit. Efficacy end points will include carbon monoxide–confirmed continuous abstinence rate (CAR) and 7-day point prevalence of abstinence. The results of this RCT will help inform medical/health authorities and physicians worldwide whether an optimally varenicline-treated cohort of T2DM patients who smoke will experience significant success rates, without significant side effects.

Trial registration NCT01387425 (https://clinicaltrials.gov/ct2/show/NCT01387425).

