### Study design

The study is a multicenter, double blind, placebo-controlled, randomized, clinical trial designed to assess the efficacy and safety of varenicline (1 mg BID) in comparison to placebo for smoking cessation in diabetic smokers. The duration of active treatment will be 12 weeks and participants will be followed up in the nontreatment phase for an additional 40 weeks (52 week timepoint). The study will consist of an initial screening visit followed by a total of 18 study visits (12 ambulatory visits and 6 telephone contact visits) (Fig. 1). The present protocol followed the SPIRIT guidelines (Fig. 2). The study will be conducted in 6 diabetic outpatient clinics of five Italian hospitals in the province of Catania (Italy, Sicily).

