### Statistical methods

#### Sample size determination

The sample size calculation for this RCT was based on success quit rates from previous smoking cessation studies [21, 33, 34]. We computed that 174 subjects (87 per each study arm) will be required to have 90% power with two-sided 0.05 significance level test to detect a difference of at least 18.7% between treatment groups for CAR 9–24 weeks. Allowing for a conservative attrition rate of approximately 40%, the target number of participants will be increased to a total of 300 (150 per each study arm).

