#### Methods of analyses

Baseline and demographic data will be listed for all treatment groups. Summary statistics will be provided for each treatment group. At baseline, differences between varenicline and placebo groups will be evaluated by means of one-way analysis of variance and Mann–Whitney *U*-test for normally and not normally distributed continuous variables, respectively; *χ*^2^ test will be used for categorical variables. The secondary endpoints will be analyzed using procedures similar to that described above for the primary endpoint. Intention-to-treat analysis will be adopted for efficacy evaluation, assuming that subjects lost to follow-up continued smoking.

Safety data will be summarized for both treatment groups and summary statistics provided.

Any events documented in the period from the point of treatment initiation until 1 week after randomized treatment has been discontinued (V14) will be considered as relevant to the safety analysis. AEs will be coded using MedDRA (Medical Dictionary for Regulatory Activities) and assigned grades based on NCI CTCAE (National Cancer Institute Common Terminology Criteria for Adverse Events). Between-groups comparisons for both individual and clustered AE rates will be carried out using χ^2^ testing or Fisher’s exact test, as appropriate.

Multiple logistic regression models will be built to identify independent predictors associated with CARs at week 12, week 24, and week 52.

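### Two stated hypotheses go beyond the design: follow-up stops 40 weeks after treatment, not one year, and difference tests of AE rates cannot show that side effects are absent

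*Protocol article*

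**What the plan says.** **Duration of abstinence.** The Abstract hypothesises that treatment will "maintain smoking abstinence up to 1 year after treatment", and the last paragraph of the Introduction repeats this. Under Study design, active treatment is 12 weeks and participants are then "followed up in the nontreatment phase for an additional 40 weeks (52 week timepoint"). Table 1 ends at V18, week 52, and the longest abstinence endpoint is CAR 9–52.

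**Safety.** Good tolerability is part of the same hypothesis. The last sentence of the Discussion says that the results will help determine whether the treated cohort "will experience significant success rates, without causing side effects". The Abstract has a milder form of this, in which only significant side effects are at issue. The method is given under Methods of analyses: "Between-groups comparisons for both individual and clustered AE rates will be carried out using" chi-square or Fisher's exact tests, alongside summary statistics. Events count from the start of treatment until one week after it stops. No margin and no expected AE rate is given.

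**Sample size.** It is set for the primary endpoint only: "174 subjects (87 per each study arm) will be required to have 90% power with two-sided 0.05 significance level test", for a "difference of at least 18.7% between treatment groups" in CAR 9–24. It is then raised to 150 per arm for attrition of about 40%.

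**The concern.** The two points share a cause: the hypothesis is worded more widely than the data and the test can reach.

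On duration, one year after treatment would run to week 12 + 52 = 64. Nothing is observed after week 52. As worded, the last 12 weeks of the hypothesis cannot be tested.

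On safety, whether a treatment is free of side effects, or of significant ones, is a question about how large an excess can be ruled out. A chi-square or Fisher test of no difference answers another question. If it is significant, it shows a difference. If it is not, it leaves open every excess that the sample was too small to detect. With no margin and no interval, the stated analysis has no result that would support a favourable answer.

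Tolerability in diabetic smokers is one of the trial's main messages to physicians and health authorities. If the wording stays as it is, a reader could take a non-significant AE comparison as evidence of no harm, and could take 40 weeks of post-treatment observation for a year.

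**Working it through.** **1. The plan's own figure.** The article gives the difference (0.187), power (90%), two-sided alpha (0.05) and n (87 per arm), but not the control rate, so the figure cannot be checked uniquely. It is attainable. With the usual formula

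n = [1.96·√(2p̄(1−p̄)) + 1.2816·√(p₁(1−p₁) + p₂(1−p₂))]² / d²

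and an assumed p₁ = 0.085, p₂ = 0.272, p̄ = 0.1785:

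- 1.96·√0.2933 = 1.061 and 1.2816·√0.2758 = 0.673
- n = (1.061 + 0.673)² / 0.187² ≈ 86.03, rounded up to 87 per arm.

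For attrition, 174/(1 − 0.40) = 290. The planned 300 corresponds to 1 − 174/300 = 42%, which is consistent with about 40% and rounding up. No fault is found here. The calculation concerns CAR 9–24 and says nothing about AEs.

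**2. Follow-up.** Treatment ends at week 12 and the last visit is week 52. That is 52 − 12 = 40 weeks after treatment, or 52 weeks from its start. The shortfall against one year after treatment is 12 weeks.

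**3. What the AE tests can detect.** Inputs are 150 per arm (Sample size determination) and a two-sided 0.05 test. The article gives no AE rates, so all rates below are assumptions and a range is shown. Fisher power is the sum of the two binomial probabilities over all tables with p ≤ 0.05. The chi-square column is the normal approximation.

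| Assumed rates | Fisher, exact | Chi-square, approx. |
|---|---|---|
| 3% vs 6% | 15% | 24% |
| 2% vs 5% | 18% | not computed |
| 5% vs 10% | 30% | 38% |
| 10% vs 15% | 21% | 26% |
| 20% vs 30% | 47% | 52% |
| 10% vs 20% | 63% | 68% |
| 5% vs 15% | 80% | 83% |
| 10% vs 25% | 92% | 93% |

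By the chi-square approximation, 80% power needs 7.5% against a background of 1%, 14.6% against 5%, 21.8% against 10%, and 34.3% against 20%.

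**4. What an interval would say instead.** If both arms show the same rate p, the 95% half-width of the risk difference is 1.96·√(2p(1−p)/150):

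- p = 5%: 4.9 points
- p = 10%: 1.96·√0.0012 = 6.8 points
- p = 20%: 9.1 points
- p = 30%: 10.4 points

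So even identical observed rates of 10% would exclude only an excess above about 6.8 points. For an event not seen at all in one arm, the upper 95% limit for its rate is 1 − 0.025^(1/150) = 2.4% two-sided, or 1 − 0.05^(1/150) = 2.0% one-sided.

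**The case against.** The case on the other side is substantial, and several parts of it stand.

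- **The sentences are aims.** A reader might infer that the article plans to conclude that there are no side effects. It does not. The Discussion says that the results will help determine whether this is so, and the Abstract is hedged in the same way. No section says that p > 0.05 will be read as no harm.
- **Low power for AEs is not an error.** The sample size is openly set for CAR 9–24, no safety power is claimed, and comparing AEs in this way is common in an efficacy trial.
- **Power is not low throughout.** A reader might infer that AE tests at 150 per arm are weak in general. They are not: large excesses in common events would probably be found, with 80% power for 5% vs 15% and 92% for 10% vs 25%. The limitation concerns uncommon events and modest excesses, and the rates are assumed.
- **Intervals may be in the SAP.** Their absence from a condensed article is not in itself a fault.
- **The one-year phrase has no analytic consequence.** The text around it gives 52 weeks correctly, and every visit and endpoint lies at or before week 52. Read as one year from the start of treatment, it fits.

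What this does not remove is a mismatch within the article. Even as an open question, absence of side effects cannot be answered in the affirmative by a difference test with no margin, which is the only comparison stated. And in its ordinary meaning, after treatment means after treatment ends, where 40 weeks are observed.

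**Conclusion.** The point holds in two limited parts.

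1. The hypothesis on duration exceeds the observation period by 12 weeks: 40 weeks after treatment against one year. This follows from the article's own figures and needs no assumption. No endpoint, visit or analysis has to change.
2. The stated AE tests cannot support the safety aim for uncommon events or modest excesses. Fisher power is about 15% to 30% for the three modest excesses taken as the main examples (3% vs 6%, 2% vs 5%, 5% vs 10%) and 63% for 10% vs 20%. It reaches 80% to 92% only for excesses of 10 to 15 points over a background of 5% to 10%. These figures rest on assumed AE rates and on all 150 per arm being analysed.

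The fault lies in how the aims fit the stated comparison. It does not lie in the sample size or in the use of chi-square or Fisher tests, and the article does not show an intention to report a null test as proof of safety.

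**What to change.** - **Abstract and Introduction:** restate the duration of abstinence as *to week 52, that is, 40 weeks after the end of treatment*.
- **Methods of analyses:** keep the chi-square and Fisher comparisons. Add the risk difference (varenicline minus placebo) with its 95% confidence interval for each pooled AE class and for SAEs. If the SAP already has this, refer to it.
- **Tolerability statement:** base it on the upper confidence limits, as the size of excess excluded over the AE analysis period, and not on non-significance.
- **Discussion and Abstract:** replace the wording on absence of side effects, in both the absolute and the milder form, with a statement of the size of excess that the data can exclude.

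The cost is small. The Results section says that conduct is complete and that data cleaning and analyses are ongoing. The changes use data already collected and add one routine set of intervals. The downside is a more modest safety statement than the present wording suggests.
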